# Tonsillectomy versus tonsillotomy for recurrent acute tonsillitis in children and adults (TOTO): study protocol for a randomized non-inferiority trial

**DOI:** 10.1186/s13063-021-05434-y

**Published:** 2021-07-22

**Keywords:** Tonsillitis, Sore throat, Tonsillectomy, Tonsillotomy, Surgery, Randomized controlled trial

## Abstract

**Background:**

Tonsillectomy is one of the most frequently performed surgeries in children and young adults worldwide. For decades, tonsillectomy was the surgical treatment of choice for recurrent acute tonsillitis. Tonsillotomy was used in some countries as an alternative to tonsillectomy only for the treatment of obstructive sleep apnea in young children. In recent years, an increase of tonsillotomy also to treat recurrent acute tonsillitis can be observed. Therefore, the German Institute for Quality and Efficiency in Health Care (IQWiG) was commissioned by the Federal Joint Committee (G-BA) to investigate whether tonsillotomy offers advantages compared to tonsillectomy. The meta-analysis of the IQWiG including studies until 2016 revealed that the long-term benefits and harms of tonsillotomy compared to tonsillectomy are unclear. Consequently, the G-BA performed a European call for a clinical trial. A consortium of the German Professional Association of ENT-surgeons (BVHNO), the German Society of Oto-Rhino-Laryngology, Head and Neck Surgery (DGHNO-KHC), and the Jena University Hospital were finally selected to perform the TOTO study.

**Methods:**

TOTO is a multicenter, 1:1 two-arm, randomized non-blinded non-inferiority trial. Four hundred fifty-four patients ≥ 3 years of age will be randomly allocated to undergo either tonsillotomy or tonsillectomy as surgical treatment of recurrent acute tonsillitis. All participants will be followed up for a total of 24 months. The primary outcome is the number of sore throat days experienced over the 24-month follow-up.

**Discussion:**

TOTO is designed to evaluate the effectiveness and efficiency of tonsillectomy versus tonsillectomy for the management of patients with recurrent acute tonsillitis. Tonsil disease and surgery have a major impact on preschool and school children as well as on economically active young adults, with individual and societal costs through loss of school visits, earnings, and productivity. If tonsillotomy is at least as effective as tonsillectomy but with reduced morbidity, this would reduce costs to the healthcare system and society.

**Trial registration:**

German Clinical Trials Register DRKS00020823. Registered on 04 September 2020.

**Supplementary Information:**

The online version contains supplementary material available at 10.1186/s13063-021-05434-y.

## Administrative information

The order of the items has been modified to group similar items (see http://www.equator-network.org/reporting-guidelines/spirit-2013-statement-defining-standard-protocol-items-for-clinical-trials/).

## Introduction

### Background and rationale {6a}

Tonsil surgery still is one of the most frequent otolaryngological surgeries, especially in children and young adults. Although the annual surgical rates have continuously declined since 2005, in 2018, still 77 tonsillectomies per 100,000 habitants and 25 adenotonsillectomies were performed [1]. At least since the publication of the Bertelsmann Foundation report “Health fact check: removal of tonsils in children and adolescents” in 2013, a new discussion about clear indication criteria for tonsillectomy was stimulated [2]. This report observed a very high regional variance in the number of tonsil surgeries. The authors could not find any medical reason justifying this variance. In parallel, the Austrian Societies of Otorhinolaryngology, Head and Neck Surgery and Paediatrics published in 2013 the results of a nationwide multicenter study on tonsil surgery based on the release of a consensus paper with clear recommendations for tonsil surgery from 2007 [3]. The aim was to restrict tonsillectomies and to promote tonsillotomy as an alternative because a series of deaths after severe post-tonsillectomy hemorrhage in children were observed in Austria in 2006 and 2007. Subsequently, a decrease of tonsillectomies could be observed and lower morbidity after tonsillotomy. In Germany, this aroused the desire for better quality assurance procedures for the indication of a tonsillectomy or a tonsillotomy. An important subsequent step was the introduction of the clinical guideline “Therapy of inflammatory conditions of the tonsils - tonsillitis” under the leadership of the German Society for Ear, Nose, and Throat, Head and Neck Surgery in 2015 [4]. This guideline defined clear recommendations for an indication for tonsil surgery in case of recurrent acute tonsillitis. A potential indication for tonsillectomy or tonsillotomy is the same in this guideline: ≥ 6 episodes of physician-diagnosed tonsillitis treated with antibiotics within the last 12 months or 3–5 episodes, if further episodes occur in the next 6 months and a total number of 6 episodes is reached. The introduction of the guideline was followed in Germany by a vigorous debate because of the strict criteria and the quasi-equation of both surgical methods. Also in 2015, the recruitment of the NAtional Trial of Tonsillectomy IN Adults (NATTINA) started in the UK [5]. NATTINA has another important focus. NATTINA is a multicenter, randomized, controlled trial for adults with recurrent tonsillitis to compare the clinical and cost-effectiveness of tonsillectomy versus conservative management. NATTINA is meanwhile closed and the results are awaited.

In 2016, the independent German Institute for Quality and Efficiency in Health Care (Institut für Qualität und Wirtschaftlichkeit im Gesundheitswesen, IQWiG) was asked by the Federal Joint Committee (G-BA) to examine whether tonsillotomy offers advantages over tonsillectomy in case of tonsil hyperplasia and obstructive sleep disorders as well as for recurrent acute tonsillitis. The resulting IQWiG report N15-11 was published in 2017 [6]. The IQWiG finally identified 19 relevant randomized controlled trials including 1590 patients. Essentially, the IQWiG report identified short-term benefits for tonsillotomy, but it was said that long-term benefits and harms are unclear. A systematic review (without meta-analysis) from 2018 screened 512 articles until April 2017 and included nine trials reporting on 770 patients [7]. The authors of this recent review concluded that the data suggest an equal efficacy of tonsillotomy and tonsillectomy in adults and a preference for tonsillotomy in terms of pain, analgesics use, patient-satisfaction, operation time, and postoperative complications.

Because of the IQWiG report, the G-BA included in 2019 tonsillotomy in the health insurance catalog for outpatient surgery for the treatment of palatine tonsil hyperplasia. On the other hand, the G-BA stated that the benefit for the treatment of recurrent acute tonsillitis is unclear and that a clinical trial is needed to provide information on long-term benefits and risks of tonsillotomy to treat recurrent acute tonsillitis. The G-BA conducted a European-wide tender for this trial. The TOTO consortium won this tender end of 2019 and was given 6 months to develop a study protocol. This protocol is presented here.

### Objectives {7}

The primary study objective is to compare the frequency of sore throat episodes within 24 months after tonsillotomy versus tonsillectomy in children and adults treated for recurrent acute tonsillitis. We hypothesize that the frequency of sore throat episodes is not higher after tonsillotomy compared to tonsillectomy. Secondary objectives are the frequency of sore throat episodes within the first 12 months after surgery, the days of incapacity of work/out of school, tonsil-specific quality of life, need for treatment with antibiotics, and need for treatment with analgesics within 24 months after surgery. Furthermore, mortality and morbidity (primary and secondary bleedings and other intraoperative and postoperative complications will be evaluated as well as the need for re-surgery within 24 months.

### Trial design {8}

This study is a multicenter, two-arm (parallel group), randomized (1:1) open-label non-inferiority trial. Patients will be randomly allocated to undergo either tonsillotomy or tonsillectomy as surgical treatment of recurrent acute tonsillitis. Additional adenoidectomy is allowed in both arms. A flowchart of the study is presented in Fig. 1.

**Fig. 1 Fig1:**
[figure not shown]
Flow chart of the trial process from allocation to follow-up. ITT, intention to treat; PP, per protocol

## Methods: Participants, interventions, and outcomes

### Study setting {9}

Patients will be recruited from twenty hospitals (in-patient and out-patient) across Germany. An up-to-date list of study sites will be published online on the TOTO homepage (https://toto-studie.hno.org/). Only study centers with at least 10 tonsil surgeries and a principal investigator with GCP certificate are eligible.

### Eligibility criteria {10}

#### Inclusion criteria

Age ≥ 3 years≥ 6 episodes of physician-diagnosed tonsillitis treated with antibiotics within the last 12 months or 3–5 episodes, if (a) further episodes occur in the next 6 months and a total number of 6 episodes is reached, or (b) there are additional patient-specific factors (special personal or professional concern, severe symptoms during the tonsillitis episodes, individual patient request) according to the German guideline for the treatment of tonsillitis [4].Subject (or parents/caregivers in case of underage participants) has provided written informed consent for participation in the study prior to any study-specific procedures

#### Exclusion criteria

Under 3 years of agePrevious tonsillotomy or tonsillectomyOther diseases of the tonsils including non-inflammatory tonsillar hyperplasia, peritonsillar abscess/quinsy, primary sleep breathing disorder, suspected malignancy, pregnant or breastfeeding, bleeding diathesis, therapeutic anticoagulation, craniofacial dysmorphism.Tonsillitis due to other reasons including mononucleosis, or insufficient knowledge of the German language to understand the questionnaires.

### Who will take informed consent? {26a}

The clinical team at the participating sites will approach and screen all children and adults who will undergo an elective (adeno)tonsillotomy or (adeno)tonsillectomy for the inclusion criteria. Potential participants will be shown the study information at their first clinic visit (unless already viewed online) and allowed to discuss the study with the designated member of the research team. Inclusion and exclusion criteria will be checked and eligible patients invited to participate in the study. Participants will be given at a minimum of 24 h to decide whether they would like to participate. Eligible patients/parents wishing to take part will be asked to provide written informed consent by signing and dating the Informed Consent Form (ICF), which will be witnessed, signed, and dated by a member of the research team. The original signed consent form will be retained in the Investigator Site File, with a copy in the clinical notes and a copy provided to the participant/parents. The study teams at each site will receive standardized, study-specific education based on standard study education materials provided by the central study administration. Notification letters about the study will be sent to relevant physicians with consultation or referral roles at study sites.

### Additional consent provisions for collection and use of participant data and biological specimens {26b}

Not applicable as no biological specimens are collected as part of this trial.

## Interventions

### Explanation for the choice of comparators {6b}

The choice of the comparators (tonsillotomy versus tonsillectomy) was predetermined by the European tender of the G-BA. The G-BA has tendered this study because the preceding assessment could not clarify if a tonsillotomy and tonsillectomy are equally efficacious in patients with recurrent acute tonsillitis and indication for tonsil surgery.

### Intervention description {11a}

Patients in the treatment arm will undergo a tonsillotomy. Tonsillotomy is defined as bilateral partial resection of the palatine tonsils. The resection is performed in such a way, that the remaining parts of the tonsil do not protrude the level of the anterior and posterior palatal arch in a non-luxated situation. Patients in the control arm will undergo tonsillectomy. Tonsillectomy is defined as a complete extracapsular resection of both palatine tonsils. An additional adenoidectomy is allowed. The following surgical techniques are allowed: cold instruments (i.e. scissors), CO_2_-laser, coblation, argon plasma coagulation, or radiofrequency ablation.

### Criteria for discontinuing or modifying allocated interventions {11b}

If the assigned type of tonsil surgery is discontinued or modified, the patient has to be excluded from the per-protocol analysis.

### Strategies to improve adherence to interventions {11c}

The participants have no influence on the adherence to both surgical interventions. Both surgeries are standard procedures for the ENT surgeons in the study centers. A variability of tonsillectomy can be excluded. To control the resection extent in tonsillotomy, the ENT surgeons in the study centers will be instructed to adhere to the resection in the level of the palatine arches.

### Relevant concomitant care permitted or prohibited during the trial {11d}

There are no relevant concomitant care and interventions that are permitted or prohibited during the trial. The use of analgesics and antibiotics is a secondary outcome measure of the trial.

### Provisions for post-trial care {30}

Not applicable as no provisions for post-trail care are part of this trial.

### Outcomes {12}

#### Primary outcome measure

The number of symptomatic sore throat episodes within 24 months after surgery, aggregated through reports of daily sore throat activity (collected once per week as patient-reported outcomes)Symptomatic sore throat episodes occur by definition when a sore throat has been reported for at least three consecutive days. Two measurements of sore throat that are at least four days apart are considered different symptomatic sore throat episodes [8]

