### Sample size {14}

Non-inferiority of a tonsillotomy compared to tonsillectomy is given when the threshold of the lower limit of the 95% confidence interval for a difference in the number of days of sore throat is above 80%. Assuming a rate of 7.56 days within 24 months in both groups, a dispersion parameter of 0.44, and a significance level of 2.5%, a negative binomial regression analysis would detect a significant difference of the quotient of the rates compared to a non-inferiority limit of 0.8 with an 80% power, if 181 participants were treated in both arms. Assuming a loss of follow-up data of 20%, 454 patients have to be randomized.

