## Statistical methods

### Statistical methods for primary and secondary outcomes {20a}

Continuous variables will be presented as means and standard deviation or median and interquartile range (IQR) if not normally distributed. Categorical data will be presented as a number with a percentage. The primary analysis is performed on the per-protocol (PP) set and sensitivity analyses in the intention-to-treat (ITT) and full analysis population are also planned.

Differences between the observed risks of events (for primary outcomes of sore throat days) between both groups will be calculated along with their 95% confidence intervals by negative binomial regression. The non-inferiority of the tonsillotomy compared to the tonsillectomy in the number of symptomatic sore throat days within 24 months is evaluated by means of negative binomial regression with the stratification factors as a covariate and the non-inferiority margin of 0.8 to a one-sided significance level of 2.5%. In secondary outcome, the number of symptomatic sore throat days within 12 months after surgery is evaluated using the negative binomial regression with the stratification factors as a covariate and the non-inferiority margin of 0.8. Other parameters like the PROM results are evaluated using analyses of covariance (ANCOVA), with the stratification variables and baseline observations as covariates. Number of days with the inability to work/attend kindergarten/school after 24 months are evaluated by negative binomial regression with stratification variables as covariates. A one-sided significance level of 2.5% will be considered statistically significant (or 5% when testing two-sided). All confirmatory analyses are fully specified in a statistical analysis plan (SAP), which is written before database lock and before unblinding the trial statistician, in order to avoid reporting bias. The results are published independently of the statistical results in order to avoid publication bias.

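### The primary endpoint is defined as sore throat episodes but sized and tested as sore throat days, so the 80% power is not established for the endpoint as defined

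*Protocol article*

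**What the plan says.** Two sets of sections in the protocol article disagree.

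**Episodes**
- Objectives {7}: the primary aim is to "compare the frequency of sore throat episodes within 24 months after tonsillotomy versus tonsillectomy". The hypothesis is worded for episodes too.
- Outcomes {12}, primary outcome measure: "The number of symptomatic sore throat episodes within 24 months after surgery". The unit is defined: "Symptomatic sore throat episodes occur by definition when a sore throat has been reported for at least three consecutive days".
- Outcomes {12}, secondary outcome measures: the 12-month outcome is a count of episodes.

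**Days**
- Abstract, Methods: "The primary outcome is the number of sore throat days experienced over the 24-month follow-up".
- Sample size {14}: the non-inferiority criterion concerns a "95% confidence interval for a difference in the number of days of sore throat is above 80" per cent, and the planning values are introduced with "Assuming a rate of 7.56 days within 24 months in both groups, a dispersion parameter of 0.44".
- Statistical methods {20a}: "the number of symptomatic sore throat days within 24 months is evaluated by means of negative binomial regression". The 12-month secondary outcome is also analysed as days.
- Participant retention {18b}: the measurement is described as days with sore throat.

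No section gives a rate or a dispersion for episodes.

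**The concern.** A non-inferiority trial with one confirmatory test needs one endpoint. Here the quantity that is formally defined has no planning rate, dispersion or model, and the quantity that is sized and tested has no definition. The outcomes section attaches the word symptomatic only to episodes, so it is unclear whether a one- or two-day sore throat adds to the symptomatic days analysed in {20a}.

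The two counts are not interchangeable. A two-day sore throat adds to days but makes no episode. A ten-day one adds ten days but a single episode. Their means and dispersions differ, so the sample size worked out for one does not carry over to the other. At stake are whether a reader can tell which result the trial committed to, and whether the stated 80% power belongs to that result.

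**Working it through.** **Inputs.** From Sample size {14}: mean 7.56 per 24 months in both arms (true ratio 1), dispersion k = 0.44, significance level 2.5%, limit 0.8, power 80%, 181 per arm, 20% loss, 454 randomized. From {20a}: the 2.5% is one-sided. From Outcomes {12}: an episode has at least three days.

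**Formula.** For a negative binomial log rate ratio with a Wald test:

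- n per arm = 2(1/μ + k)(1.960 + 0.8416)² / (ln 0.8)²
- power = Φ(0.2231 / SE − 1.960), with SE = √[2(1/μ + k)/n]

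|ln 0.8| = 0.2231. A limit of 1/0.8 = 1.25 has the same absolute logarithm, so the orientation of the ratio does not affect these figures.

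**Step 1: the plan's own figure.** 1/7.56 + 0.44 = 0.1323 + 0.44 = 0.5723. Then n = 2 × 0.5723 × 7.849 / 0.04979 = 180.4, rounded up to 181. Power at 181 is 80.1%. For loss, 181/0.8 = 226.25, so 227 per arm and 454 in total. Both stated figures reproduce, for inputs labelled as days.

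**Step 2: the largest episode mean consistent with those inputs.** Each episode uses at least three days, so the mean is at most 7.56/3 = 2.52.

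**Step 3: power on episodes at mean 2.52 and 181 per arm.** 1/2.52 = 0.3968.

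| Episode dispersion | 1/μ + k | SE | Power |
|---|---|---|---|
| 0.175 | 0.572 | 0.0795 | 80% |
| 0.44 | 0.837 | 0.0962 | 64% |
| 0.6 | 0.997 | 0.1050 | 57% |

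The dispersions are assumptions, because the documents give none for episodes. The first follows if every sore throat day falls in an episode of exactly three days. Days are then three times episodes, both have the same squared coefficient of variation (0.5723), and k = 0.5723 − 0.3968 = 0.175. The second carries the day value over unchanged.

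**Step 4: check by simulation.** Fitted negative binomial regressions, 1,500 data sets per case with 181 per arm, gave 79.9% for days, 64.5% for episodes at 0.44 and 79.8% for episodes at about 0.175.

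**Step 5: the other possibility.** If 7.56 and 0.44 really describe episodes, Step 1 applies as it stands and power is 80%. The unit in the abstract, sample size and analysis sections would then be the error.

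**The case against.** A reader might infer that the trial has at most 64% power on episodes. The strongest objection is that the documents do not support this, and that objection stands. The 0.44 is given for days only. Combining 0.44 with a mean of 2.52 three-day episodes would imply a day dispersion of 0.3968 + 0.44 − 0.1323 = 0.70, not the stated 0.44. More generally, suppose that all sore throat days lie within episodes and that episode length L is independent of episode count. Then CV²(days) = CV²(episodes) + Var(L)/(mean count × (mean L)²). The episode CV² cannot exceed 0.572, and power on episodes would be about 80% or better. Lower power needs something else, such as many isolated one- or two-day sore throats outside episodes, or length related to count. Either is possible, but the documents do not describe it.

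A second objection is that selective choice of endpoint is restrained. Section {20a} promises an analysis plan written before database lock and before the statistician is unblinded. Section {17a} adds a strict evaluation algorithm and an endpoint committee. That plan is not shown and may name one endpoint. This also stands as far as it goes: the text gives no ground for saying that the endpoint will be picked after arm-level results are known. Nor does it give figures showing that one count would favour one arm.

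Neither objection reconciles the sections. Condensing a full protocol into an article explains omissions, but not two opposing statements of the primary endpoint.

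**Conclusion.** The contradiction is in the current text and rests on no assumption: episodes in the objective and the outcome definition, days in the abstract, sample size and confirmatory analysis, with the same split for the 12-month secondary outcome. It must be resolved.

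The conclusion on power is narrower. The 80% with 181 per arm is shown only for a mean of 7.56 and a dispersion of 0.44 labelled as days, and it is not established for the defined endpoint. The range of 80% to 57% in the working shows how strongly power depends on an unstated dispersion. It is neither an estimate nor a bound, and 64% is not a ceiling. It would be wrong to conclude that the trial is underpowered. If 7.56 is a mislabelled episode count, the stated power is correct.

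**What to change.** Before database lock, and while the statistician is blinded, name one primary endpoint and confirm from the planning source whether 7.56 and 0.44 refer to days or to episodes. Then use the same term in the Abstract, Objectives {7}, both parts of Outcomes {12}, Sample size {14}, participant retention {18b} and Statistical methods {20a}, including the 12-month outcome.

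- **If days:** define which days count as symptomatic, in particular whether isolated one- or two-day sore throats do, and keep episodes as a secondary outcome.
- **If episodes:** rewrite the analysis for episodes and restate the power at the planned sample size from a justified episode rate and dispersion, with a range. If the planning values prove to be for episodes, only the unit needs correcting.

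The choice belongs to the sponsor and should rest on the clinical question. That one count happens to be already sized is not a sufficient reason.

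**Cost:** a formal protocol amendment with ethics approval, as the amendments section {25} requires for changes to objectives, and matching wording in the analysis plan and registration. Enrolment does not change. If episodes are kept, the restated power may differ from 80%.
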